### Participant timeline {13}

Please see Fig. 1 for details of the participant timeline. Details of the schedule for enrolment, interventions, and assessments can be found in Table 1.

**Fig. 1 Fig1:**
[figure not shown]
Participant timeline

**Table 1 Tab1:** Schedule of enrolment, interventions, and assessments

	**STUDY PERIOD**									
**Timepoint**	***−Day ***_***28***_	***Week 1***	***Week 3***	***Week 5***	***Week 7***	***Week 9***	***Month 3***	***Month 6***	***Month***** 9**	***Month***** 12**
**Visit window(days)**		***Day***_***1~7***_	***± 3***	***± 3***	***± 3***	***± 3***	***± 7***	***± 7***	***± 7***	***± 7***
**Enrolment:**										
***Eligibility screen***										
***Informed consent***	X									
***Baseline***	X									
***Laboratory test***	X									
***CT scans***	X									
***Allocation***	X									
**Interventions:**										
**control arm****: *****surgery alone***		X								
**Neoadjuvant arm****: *****TACE***		X								
***Camrelizumab***		X	X	X	X					
***Apatinib***		X	X	X	X					
**Safety assessments:**										
***Adverse events***		X	X	X	X	X				
***Living state***			X	X	**X**	**X**	X	X	**X**	**x**
**Assessments:**								X		
***Lab, CT******, ******etc***						X				
***Primary endpoint***										**X**
***Secondary endpoint***							X			**X**

### Sample size {14}

The sample size was performed using the software PASS (version 2015). The calculation is based on the primary endpoint which is RFS in the present study. Previous research data showed that the 1-year RFS rate was 40% for patients with a single huge HCC after surgery [9]. Our prior study showed that the 1-year event-free survival (EFS) rate was 65% for patients with unresectable HCC after receiving a similar treatment regime [22]. Therefore, we hypothesize that neoadjuvant therapy could increase the 1-year RFS rate to 70% for patients with a single huge HCC. Using an alpha of 0.025 at one-sided, a power of 80%, a total of 60 participants needed to be enrolled with 30 in each arm when considering an attrition rate of 10% and an anticipated recruitment period of 1.5 years.

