**Methods:**

This multi-center, open-label randomized phase 3 trial will be conducted at 7 tertiary hospitals. Patients with single huge (≥ 10 cm in diameter), resectable HCC will be randomly assigned in a 1:1 ratio to arm of surgery alone or arm of neoadjuvant therapy followed by surgery. In the neoadjuvant therapy group, patients will receive TACE within 1 week after randomization, followed by camrelizumab (200 mg q2w, 4 cycles), along with apatinib (250 mg qd, 2 months). Patients will receive liver resection after neoadjuvant therapy unless the disease is assessed as progressive. The primary outcome is recurrence-free survival (RFS) at 1 year. The planned sample size of 60 patients will be calculated to permit the accumulation of sufficient RFS events in 1 year to achieve 80% power for the RFS primary endpoint.

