### Trial design {8}

The study is a prospective, multicenter, open-label, randomized controlled trial. Patients will be randomly assigned in a 1:1 ratio to either the experimental group (surgery after neoadjuvant treatment with TACE combined with camrelizumab and apatinib) or the control group (surgical resection without neoadjuvant treatment), using a parallel design with superiority.

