### Recruitment {15}

We aim to enroll a total of 60 participants across seven hospitals. To achieve this, monthly online conferences are scheduled to monitor enrollment progress at each hospital and strategize methods to accelerate recruitment. Participants at each center will be contacted via telephone. All seven centers are expected to collectively recruit approximately 3–4 participants per month, with an anticipated recruitment period of 1.5 years. The study will run from January 2024 to June 2026.

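### The sample size of 60 and the 1-year primary endpoint do not match: 80% power needs RFS events after Month 12, but the plan ties it to events within 1 year

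*Protocol article*

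**What the plan says.** All places are in the protocol article.

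- **Sample size {14}** bases the calculation on RFS. It takes from earlier research that "the 1-year RFS rate was 40% for patients with a single huge HCC after surgery" and supposes that "neoadjuvant therapy could increase the 1-year RFS rate to 70" (per cent). The error rates are "Using an alpha of 0.025 at one-sided, a power of 80" (per cent). The result is that "a total of 60 participants needed to be enrolled with 30 in each arm when considering an attrition rate of 10" (per cent). The same sentence goes on to name a recruitment period of 1.5 years as a further input.
- **Trial design {8}** fixes the allocation: "Patients will be randomly assigned in a 1:1 ratio".
- **Abstract, Methods** says the sample size will "permit the accumulation of sufficient RFS events in 1 year to achieve 80% power for the RFS primary endpoint".
- **Outcomes {12}** names the 1-year RFS rate as primary, but then defines it as a time from randomisation to recurrence or death.
- **Table 1** ends at Month 12, and its row "Primary endpoint" is marked there.
- **Recruitment {15}** states: "The study will run from January 2024 to June 2026". That is 1.5 years of recruitment plus 1 year.
- **Statistical methods {20a}** plans Kaplan-Meier estimates and Cox models in all randomised patients, with no cut at 12 months.

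**The concern.** Two accounts of the primary comparison stand side by side. The abstract, the name of the endpoint and the visit schedule describe a comparison over the first 12 months. The recruitment period among the sample-size inputs, the June 2026 close and the Cox model describe a time-to-event comparison that also uses later events. These carry different information: about 24 to 27 events under the first and about 35 to 36 under the second.

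If the trial is analysed as the abstract describes, a true 30-point gain in 1-year RFS would be missed in roughly 3 to 4 of 10 such trials, not the stated 2 of 10. A null result in a phase 3 trial would then be read against power that the design lacks. While the window is unsettled, it could also be chosen after data have been seen.

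**Working it through.** **Inputs.** 1-year RFS 40% and 70%, one-sided alpha 0.025, power 80%, 60 patients, 10% attrition, 1.5-year recruitment (Sample size {14}); 1:1 allocation (Trial design {8}); study length 2.5 years (Recruitment {15}). Assumed, because the article does not say: exponential survival with proportional hazards, uniform accrual, and the timing of the 10% attrition.

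**Step 1. Events needed.**
HR = ln 0.70 / ln 0.40 = 0.389, so ln HR = −0.9435.
Schoenfeld: 4(1.960 + 0.842)² / 0.9435² = 35.3 events.
Freedman: (1.960 + 0.842)² × [(1 + 0.389)/(1 − 0.389)]² = 40.6 events.

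**Step 2. Reproducing 60: all events to June 2026.**
With accrual A = 1.5 years, minimum follow-up F = 1 year, event hazard λ (0.916 control, 0.357 experimental), loss hazard g and t = λ + g:
P(event) = (λ/t) × {1 − [exp(−tF) − exp(−t(F + A))]/(tA)}.

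| Attrition as censoring | P(event), control / experimental | Mean | Events from 60 | N for 35.3 events | Power at 60, Schoenfeld | Power at 60, Freedman |
|---|---|---|---|---|---|---|
| 10% over 2.5 years (g = 0.042) | 0.762 / 0.443 | 0.602 | 36.1 | 58.6 | 81% | 75% |
| 10% per year (g = 0.105) | 0.732 / 0.421 | 0.576 | 34.6 | 61.2 | 79% | 73% |

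Schoenfeld power is Φ(½√d × 0.9435 − 1.960). Freedman power is Φ(√d × 0.4396 − 1.960), where 0.4396 = (1 − 0.389)/(1 + 0.389). By Schoenfeld, the plan's 60 and 80% are both recovered.

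If the 10% are instead removed outright, 54 patients give 54 × 0.620 = 33.5 events and power of 78% (Schoenfeld) or 72% (Freedman). That is harsher than the planned analysis of all randomised patients, in which a patient who drops out contributes until censored.

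**Step 3. The 1-year window as stated.**
The mean 1-year event probability is (0.60 + 0.30)/2 = 0.45. It comes directly from the two stated rates and needs no exponential shape.

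| Patients | Events by 12 months | Schoenfeld | Freedman | Two proportions |
|---|---|---|---|---|
| 54 (60 less 10%) | 54 × 0.45 = 24.3 | 64% | 58% | 61% |
| 60 (no loss) | 60 × 0.45 = 27.0 | 69% | 63% | 65% |

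No method reaches 70%, even with no attrition.

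**Step 4. What 80% power would take on the 1-year window.**
Two proportions: n per arm = {[1.960√(2 × 0.55 × 0.45) + 0.842√(0.24 + 0.21)]/0.30}² = 42.0, so 42 evaluable per arm against 27 in the plan.
Log-rank: 35.3/0.45 = 78 to 40.6/0.45 = 90 evaluable. Dividing by 0.9 gives about 87 to 100 enrolled; 84/0.9 = 93 for two proportions.
With 27 evaluable per arm, the two-proportion test has about 80% power for 40% against 77%.

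**The case against.** A reader might infer from Step 3 that 60 is an arithmetic error and that the plan's own inputs give only 60–65% power. The document does not support that. A recruitment period plays no part in a two-proportion test or a fixed 12-month event count; it matters only when entry is staggered and follow-up runs to a common close. The article lists it as an input, gives a close 1 year after recruitment ends, defines RFS as a time to event and analyses it by Cox regression without truncation. On those inputs 60 is recovered. This part of the objection stands, and it rules out calling 60 a proven miscalculation.

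It can also be said that the 12-month limit is inferred from an abstract phrase, an endpoint label and the last column of a condensed table. A mark at Month 12 does not say that later events are discarded. Post-trial care {30} foresees regular follow-up, and the mid-term analysis {21b} is timed from the last enrolment, when the earliest patients would be about 2 years from entry. That is fair as far as it goes. But the abstract's power statement is explicit about 1 year, no RFS assessment after Month 12 is scheduled, and the June 2026 close fits equally well with simply giving the last patient 12 months. The objection shows that a design with about 80% power exists; it does not show that this is the design described.

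**Conclusion.** The point holds as a mismatch between the endpoint window and the basis of the sample size. Events to June 2026 support 60 patients at 79–81% power by Schoenfeld (73–75% by Freedman). Events within 1 year number about 24 to 27 against the 35 to 41 needed, and give about 58–69% power depending on method and attrition. The 80% claim and the stated 1-year endpoint cannot both stand with 60 patients.

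The long-follow-up figures rest on exponential survival, uniform accrual and losses acting as uninformative censoring. The 12-month event counts and the two-proportion figures rest only on the two stated rates and the attrition allowance; the log-rank powers on that window also need proportional hazards. The inconsistency should be settled before any outcome comparison, because it decides what a null result would mean.

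**What to change.** Choose one comparison and make the abstract, Sample size {14}, Outcomes {12}, Table 1 and Statistical methods {20a} agree with it. Neither option adds patients.

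**(a) Time-to-event primary test.** Specify a log-rank or Cox comparison of all RFS events to the June 2026 close. Schedule RFS assessments after Month 12 for patients enrolled early. State a target of about 35 events, with power just under or about 80% by Schoenfeld, and give the accrual and loss assumptions. Remove the words that confine the events to 1 year from the abstract's power statement. Cost: longer follow-up of early enrollees, within the study period already planned.

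**(b) 1-year primary comparison.** Keep the 1-year RFS rate and restate its power as about 60–69%, or as 80% power for about 40% against 77% with 27 evaluable per arm. Withdraw the 80% claim for 40% against 70%. Cost: a less favourable stated power.

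Option (a) keeps the stated power close to what the calculation appears to have assumed.

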### Recruitment {15}

We aim to enroll a total of 60 participants across seven hospitals. To achieve this, monthly online conferences are scheduled to monitor enrollment progress at each hospital and strategize methods to accelerate recruitment. Participants at each center will be contacted via telephone. All seven centers are expected to collectively recruit approximately 3–4 participants per month, with an anticipated recruitment period of 1.5 years. The study will run from January 2024 to June 2026.

## Assignment of interventions: allocation

### Sequence generation {16a}

Participants will be randomly assigned to the arm of surgery alone or the arm of neoadjuvant therapy followed by surgery in a 1:1 ratio, using SAS statistical software.

### Concealment mechanism {16b}

The generated random allocation sequence will be sealed in sequentially numbered, opaque envelopes, with each participant’s random number remaining unchanged throughout the study. Envelopes will be opened only when eligible study subjects agree to participate.

### Implementation {16c}

The allocation sequence is generated by the trial statistician, [name]. Participants are enrolled by the study team and assigned to the intervention by the trial investigators.

## Assignment of interventions: blinding

### Who will be blinded {17a}

Data analysts are blinded to the interventions and will not participate in patient enrollment or medical care. It is not possible to blind trial participants, care providers, or investigators due to the complexity of the neoadjuvant therapy.

### Procedure for unblinding if needed {17b}

Since study team members are unblinded, members who participate in patient enrollment and trial intervention will not complete data collection or outcome assessments during the trial. As participants are not blinded, there is no further procedure for unblinding participants.

## Data collection and management

### Plans for assessment and collection of outcomes {18a}

All investigators and coordinators will receive specialized training for data collection. Baseline assessments will be conducted before randomization. Any AE during neoadjuvant therapy will be assessed and managed by investigators and recorded timely. Tumor response after neoadjuvant therapy will be performed via enhanced CT using the response evaluation criteria in solid tumors, version 1.1 (RECIST 1.1), and the modified response evaluation criteria in solid tumors (mRECIST) in 2 weeks after neoadjuvant therapy. Perioperative data, including intraoperative information and postoperative complications which will be graded by Clavein-Dindo criteria, will be recorded before discharge.

### Plans to promote participant retention and complete follow-up {18b}

Participants will receive ¥100 per trial visit as reimbursement for their time. If a participant chooses to withdraw from the trial, reasons for withdrawal will be recorded but no further outcome data will be collected.

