### Criteria for discontinuing or modifying allocated interventions {11b}

Discontinuation or modifying of the allocated intervention is possible after a participant withdraws from the intervention and/or trial or based on clinical judgment by the intervention facilitator, e.g., when a participant is unable to continue due to adverse event (AE) caused by camrelizumab and/or apatinib.

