### Outcomes {12}

The primary endpoint is the 1-year RFS rate, defined as the time period from randomization to the first documented HCC recurrence or death from any cause. The key secondary endpoints include pathological remission degree and OS which was defined as the time period from randomization to death from any cause. Pathological complete remission (pCR) is defined as existent ≤ 1% active tumor cells, while major pathological remission (mPR) is defined as ≤10% active tumor cells. Safety outcomes encompass adverse events (AEs), defined as the occurrence of ≥ 3 grade hematological or non-hematological toxicities (including but not limited to liver dysfunction, hematological abnormalities, hypertension, diarrhea, proteinuria, hand-foot syndrome, etc.). The severity of adverse events will be graded according to the Common Terminology Criteria for Adverse Events (CTCAE v5.0).

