## Statistical methods

### Statistical methods for primary and secondary outcomes {20a}

Primary efficacy will be assessed in all randomized patients using the intention-to-treat (ITT) principal. And the safety analysis will include all participants who received at least one post-randomization measure. Kaplan-Meier method is used to determine RFS and OS. Hazard ratios (HRs) with 95% confidence intervals (CIs) are estimated using Cox proportional risk models. Continuous variables are analyzed using either unpaired Student’s *t*-test or the Mann-Whitney *U* test, while categorical data are assessed using the chi-square test or Fisher’s exact test, as appropriate. Data analysis will be performed using SPSS version 26.0 and *P* values < 0.05 are considered statistically significant. The flow of participants screened by the trial and trial results will be reported according to Consolidated Standards of Reporting Trials (CONSORT).

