### Methods in analysis to handle protocol non-adherence and any statistical methods to handle missing data {20c}

As we target the treatment regimen estimate, we will include all participants in the primary analysis including those who do not adhere to the protocol. A supplementary analysis will be performed using a per-protocol principal to estimate the treatment effect for those who switch to another arm after randomization. Participants who have missing data points will be included in the analysis under a Missing at Random assumption implicit when using the longitudinal model.

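### Outcome collection ends when a participant withdraws from the trial, even if they would allow recurrence and survival status to be collected, which undermines the all-randomized analysis

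*Protocol article*

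**What the plan says.** Section {18b} of the protocol article, on retention and complete follow-up, sets the rule for a participant who withdraws from the trial: "reasons for withdrawal will be recorded but no further outcome data will be collected". It does not exempt recurrence or vital status and does not provide for asking the participant to allow follow-up through records or by telephone.

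The analysis sections ask for more than this rule delivers:

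- Section {20a}: "Primary efficacy will be assessed in all randomized patients using the intention-to-treat (ITT) principal". For the time-to-event outcomes, "Kaplan-Meier method is used to determine RFS and OS", with hazard ratios from Cox models.
- Section {20c} targets a treatment-regimen estimate: "we will include all participants in the primary analysis including those who do not adhere to the protocol". Participants with missing data points are included "under a Missing at Random assumption implicit when using the longitudinal model".
- Section {12} describes RFS as "defined as the time period from randomization to the first documented HCC recurrence or death from any cause". Overall survival (OS) also runs from randomization.

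Section {11b} allows the intervention to be discontinued or modified "after a participant withdraws from the intervention and/or trial", so it names the two kinds of withdrawal separately. Section {17a} says that participants, care providers and investigators are not blinded.

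**The concern.** A treatment-regimen estimate in all randomized patients compares what happens to everyone assigned to each arm, whatever course they then follow. It needs recurrence and death recorded after a patient leaves the assigned course. Section {18b} gives up that information for anyone who leaves the trial, including those who would have let the team check their records.

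Under Kaplan-Meier and Cox, such patients can only be censored at last contact. That is harmless if leaving is unrelated to prognosis. In an open-label trial it may not be. Control patients are to be operated on within a week of randomization, while the neoadjuvant arm faces about two months of treatment before surgery, so the occasions and motives for leaving can differ by arm. The missing-data sentence in {20c} does not help, because it relies on a longitudinal model and the methods named for RFS and OS contain none.

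With 30 patients per arm, a few such losses can move the result, and outcomes that were never collected cannot be restored at the analysis stage.

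**Working it through.** **Inputs from the article.** 1-year RFS 40% (control) and 70% (neoadjuvant); one-sided alpha 0.025; power 80%; 60 patients, 30 per arm; attrition 10%; recruitment 1.5 years (all section {14}). The study runs from January 2024 to June 2026 (section {15}), which is about 1 year after the last entry. Assumptions not in the article: exponential RFS, uniform accrual, and the timing and pattern of withdrawals.

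**1. The plan's own figure.**
- Hazard ratio = ln 0.70 / ln 0.40 = 0.389.
- Events (Schoenfeld) = 4 × (1.960 + 0.842)² / (ln 0.389)² = 35.3, so 36.
- Mean event probability with 1.5 years' accrual and 1 year's minimum follow-up = 0.620, so N = 35.3/0.620 = 57 to 36/0.620 = 58 before attrition.
- With loss of 10% over 2.5 years, N = 58.6 to 59.8. The stated 60 is reproduced within 2 patients, provided that events after 1 year count.

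**2. What attrition costs in precision.** At 60 patients:

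| Scenario | Expected events | Power |
|---|---|---|
| Outcomes collected on everyone | 37.2 | 82% |
| Loss of 10% per year | 34.6 | 79% |
| 10% contribute nothing (54 left) | 33.5 | 78% |

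So the planned attrition costs about 3 to 4 points of power. The sample-size allowance deals with that loss. It does nothing about bias.

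**3. Worst-case bounds on the 1-year difference.** 10% of 60 is 6 patients, or 3 per arm if balanced, leaving 27 per arm. If those observed show 40% and 70%:
- Lowest: (0.70 × 27)/30 − (0.40 × 27 + 3)/30 = 0.63 − 0.46 = 0.17.
- Highest: (0.70 × 27 + 3)/30 − (0.40 × 27)/30 = 0.73 − 0.36 = 0.37.

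In whole patients, with chi-square p-values (uncorrected) as illustration only:

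| Case | Control | Neoadjuvant | Difference | p |
|---|---|---|---|---|
| Observed | 11/27 | 19/27 | 29.6 points | 0.028 |
| Least favourable | 14/30 | 19/30 | 16.7 points | 0.19 |
| Most favourable | 11/30 | 22/30 | 36.7 points | 0.004 |

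Each lost patient can move an arm's 1-year rate by up to 1/30 = 3.3 points.

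**4. Stress test of the censoring.** This is a log-rank simulation truncated at 1 year, with 30 per arm and 8,000 runs. The extreme assumption is that every withdrawer would have had an event within the year. The ranges cover two timings of withdrawal: just before the event, or at a random earlier time.

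| Withdrawals, true RFS 40% in both arms | One-sided type I error | Effect on Kaplan-Meier rate |
|---|---|---|
| None | about 0.027 | none |
| 3, neoadjuvant arm only | about 0.07 | that arm reads about 46% |
| 6, neoadjuvant arm only | 0.16 to 0.20 | that arm reads 52 to 54% |
| 3, control arm only | about 0.01 | that arm reads about 46% |
| 3 in each arm | 0.027 to 0.029 | both arms 5 to 7 points too high |

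A hand check agrees. 18 of 30 patients are expected to have an event, and hiding 3 of them just before the event gives 0.40^(15/18) = 0.466.

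Under a true 40% versus 70%, simulated power on this 1-year comparison is about 0.67. It becomes about 0.86 if the 3 withdrawals are all in the neoadjuvant arm and 0.46 to 0.49 if all are in the control arm. The direction of the bias therefore depends on who leaves.

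**The case against.** Most of the case against concerns how far the rule reaches, and much of it stands.

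- **Stopping treatment.** A reader might infer that a patient who stops camrelizumab or apatinib for toxicity is no longer followed. The article does not say so. {18b} applies to withdrawal from the trial, {11b} names withdrawal from the intervention and from the trial separately, and {20c} keeps non-adherers in the primary analysis.
- **Defeat of the ITT analysis.** A reader might also infer that the analysis fails outright. Withdrawers stay in the analysis set and contribute time until they are censored, so the damage is in proportion to their number.
- **Informative censoring as a certainty.** The documents give no withdrawal pattern. Bias needs leaving to be related to prognosis, and distortion of the comparison generally needs that relation to differ by arm. Balanced losses in the stress test left type I error essentially unchanged.
- **The bounds.** They treat all attrition as withdrawal, although {14} does not define attrition and it may include ordinary loss to follow-up. They give no credit for follow-up before withdrawal, and they assume opposite outcomes for the lost patients in the two arms. They are an upper limit on what rewording {18b} could recover.
- **Consent and condensation.** Ending collection when a participant refuses any further use of data is legitimate, and tiered withdrawal options are detail that an article may leave to the full protocol and consent form.

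The last point does not remove the concern. The article is not silent: it states a rule without exception, and that rule, followed as written, discards outcomes that some participants would have allowed to be collected.

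**Conclusion.** The concern holds in a limited form. The stop on outcome collection after trial withdrawal undermines, without defeating, the all-randomized treatment-regimen analysis of RFS and OS. Informative censoring is a plausible risk in an open-label trial with very different patient pathways, and is not shown to occur.

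As a worst case only, the planned 10% attrition would leave the true 1-year difference anywhere from 17 to 37 points around an observed 30. This assumes that all of the attrition is withdrawal, split 3 and 3, with nothing known about those patients' 1-year status. That is enough to change the conclusion in a trial of this size. The type I error of about 0.07 rests on a still more extreme assumption, with all 3 losses in one arm and every one of them a hidden event. It is a stress case and not a forecast.

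The change is worth making because it is cheap, respects refusal, and cannot be made good after the data have been missed.

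**What to change.** Replace the sentence in {18b}. A participant who withdraws is asked to agree to continued collection of recurrence and survival status, from clinic records or by telephone, and collection stops only if this is refused. Record whether the withdrawal is from treatment, from visits or from data collection, so that the split already named in {11b} carries through to the data.

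The cost is one protocol and consent amendment, one case report form field and a small amount of extra contact. That contact is new work: the individual calls in {11c} serve adherence and the telephone contact in {15} serves recruitment, and neither is planned for outcomes after withdrawal. Recruitment had already begun when the article was written, so the amendment gains most if made early. Participants who refuse, and those lost without contact, will still be missing.
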